## Abstract

**Background:**

IgA nephropathy (IgAN) is one of the most common primary glomerular diseases worldwide, but effective therapy remains limited and many patients progress to end-stage renal disease (ESRD). Only angiotensin-converting enzyme inhibitors (ACE-I)/angiotensin-receptor blockers (ARB) show a high level of evidence (1B level) of being of value in the treatment for IgAN according to the 2012 Kidney Disease: Improving Global Outcomes (KDIGO) guidelines. However, traditional Chinese medicine has raised attention in kidney disease research. *Abelmoschus manihot*, a single medicament of traditional Chinese medicine has shown therapeutic effects in primary glomerular disease according to the randomized controlled clinical trial that we have completed. Here, we conduct a new study to assess the efficacy and safety of *Abelmoschus manihot* in IgAN. Also, this study is currently the largest double-blind, randomized controlled registered clinical research for the treatment of IgAN.

**Methods:**

We will conduct a multicenter, prospective, double-blind, double-dummy randomized controlled study. The study is designed as a noninferiority clinical trial. Approximately 1600 biopsy-proven IgAN patients will be enrolled at 100 centers in China and followed up for as long as 48 weeks. IgAN patients will be randomized assigned to the *Abelmoschus manihot* group (in the form of a *huangkui* capsule, 2.5 g, three times per day) and the losartan potassium group (losartan potassium, 100 mg/d). The primary outcome is the change in 24-h proteinuria from baseline after 48 weeks of treatment. Change in estimated glomerular filtration rate (eGFR) from baseline after 48 weeks of treatment, the incidence of endpoint events (proteinuria ≥3.5 g/24 h, the doubling of serum creatinine, or receiving blood purification treatment) are the secondary outcomes. Twenty-four-hour proteinuria and eGFR are measured at 0, 4, 12, 24, 36 and 48 weeks.

**Discussion:**

This study will be of sufficient size and scope to evaluate the efficacy and safety of *Abelmoschus manihot* compared to losartan potassium in treating patients with IgAN. The results of this study may provide a new, effective and safe treatment strategy for IgAN.

**Trial registration:**

ClinicalTrials.gov, identifier: NCT02231125. Registered on 30 August 2014.

**Electronic supplementary material:**

The online version of this article (doi:10.1186/s13063-016-1774-6) contains supplementary material, which is available to authorized users.

## Background

IgA nephropathy (IgAN) is the most common primary glomerular disease worldwide, and it is an important cause of chronic kidney disease (CKD) and end-stage renal disease (ESRD) [1, 2]. IgA nephropathy is also the most common primary glomerular disease and the leading cause of ESRD in China [3]. Kidney Disease: Improving Global Outcomes (KDIGO) Clinical Practice Guideline for Glomerulonephritis recommends angiotensin-converting enzyme inhibitors (ACE-I)/angiotensin-receptor blocker (ARB), corticosteroids, and immunosuppressive agent treatment according to the level of the urinary protein and renal function of IgAN patients [4]. Since current therapy of IgAN is limited and most treatments have little evidence to recommend them, it is necessary to explore novel, effective and safe treatment for IgAN patients. Traditional Chinese medicine (TCM) has a long history in treatment of chronic kidney disease (CKD), and a growing number of studies have confirmed that TCM has the curative effect of reducing urinary protein, protecting kidney function [5]. *Abelmoschus manihot* (AM) extracted from *Flos Abelmoschus manihot*, a single medicament of TCM has been widely used to treat chronic kidney diseases, such as IgAN, membranous nephropathy and diabetic nephropathy, and has shown the effects of reducing proteinuria and protecting kidney function [6–8]. ACE-I and ARB drugs are commonly used to treat proteinuria, and the range of reduction is reportedly 30–50% in adults [9, 10]. Thus, we use losartan as the positive control. We have finished a randomized controlled trial (RCT) to assess the efficacy and safety of AM in patients with primary glomerular disease. The clinical research enrolled a total of 417 patients from 26 hospitals who had been diagnosed with primary glomerular disease by renal biopsy. The results showed that AM can significantly reduce urinary protein in patients with primary kidney disease (CKD stages 1–2) and its effect is better than that of losartan potassium (50 mg/d) [11]. Since IgAN was the most common primary glomerular disease and the design of the former study had some limitations, such as not using a blind method, the low dose of losartan potassium (50 mg/d) used, and a short observation time (24 weeks), we conducted this prospective, double-blind, double-dummy randomized controlled study to evaluate efficacy and safety of AM in the treatment of IgAN.

## Methods

### Objectives

The objective of the trial is to assess the clinical effects and safety of AM in IgAN patients.

### Trial design

This study is a multicenter, prospective, double-blind, double-dummy RCT. The study is designed as a noninferiority clinical trial. The hypothesis is that AM significantly reduces the urinary protein levels of IgAN patients and that its curative effect is not inferior to that of losartan potassium (100 mg/d) after 48 weeks of treatment. We have followed the Standardised Protocol Interventions: Recommendations for Interventional Trials (SPIRIT) 2013 Statement which defines standard protocol items for clinical trials [12]. See the items in Fig. 1 and Additional file 1 for the Checklist. The study protocol was designed by members of the Executive Committee (composed of the Department of Kidney Disease of Chinese People’s Liberation Army General Hospital, Peking University Clinical Research Institute). The protocol is being implemented by the study group comprising 100 clinical centers across China. The network database was designed by the Executive Committee. Venturepharm CRO Service Group which provides the clinical research associate service.

**Fig. 1 Fig1:**
[figure not shown]
Trial flow diagram

### Setting and participants

Approximately 1600 biopsy-proven IgAN patients will be enrolled at 100 centers in China and followed up for as long as 48 weeks.

### Eligibility, exclusion and exit criteria

The inclusion criteria are: (1) diagnosis of IgAN by kidney biopsy, (2) age 18 to 65 years, (3) blood pressure of ≤140/90 mmHg, (4) estimated glomerular filtration rate (eGFR) ≥45 ml/min/1.73 m^2^ (calculated with the use of the CKD-EPI Creatinine Equation 2009) [13], (5) 24-h proteinuria range of between 0.5 and 3.0 g, (6) agreement to participate and provision of signed informed consent. Additional file 2 shows the Informed Consent Form in more detail. The exclusion criteria are: (1) secondary IgAN, (2) allergy to AM or losartan potassium, (3) history of AM and ACE-I and/or ARB use within the last 6 months, (4) history of glucocorticoid, immunosuppressant, or *Tripterygium* drug use within the previous 1 year, (5) blood pressure of <90/60 mmHg, (6) serum potassium >5.5 mmol/L, (7) serum albumin <30 g/L, (8) unilateral or bilateral renal artery stenosis, (9) pregnant or lactating women, (10) severe heart, brain, liver, or hematopoietic system disease, or other serious illnesses that may affect survival, (11) participation in another clinical investigation. The exit criteria are: (1) endpoint event: proteinuria ≥3.5 g/24 h, doubling of serum creatinine, or receiving blood purification treatment, (2) blood pressure of >160/90 mmHg after antihypertensive drug combination therapy (convinced by measuring blood pressure three times within 2 weeks), (3) blood pressure of <90/60 mmHg after stopping using other antihypertensive agents, (4) serum potassium >5.5 mmol/L after antihyperkalemia drug treatment, (5) serum creatinine rapidly rising to >50% of the baseline within 4 weeks after treatment, (6) serious adverse events (SAEs): hospitalization (initial or prolonged), disability or permanent damage, life-threatening, death, congenital anomaly/birth defect and other serious events (important medical events) [14], (7) serious breach of protocol: participants failing to take medications according to protocol or taking some drugs that have a significant impact on the primary and secondary outcomes during the 48-week observation period, (8) loss to follow-up or withdrawal from the trial, (9) pregnancy during the trial.

### Interventions

*Abelmoschus manihot* (AM) group: a *huangkui* capsule given orally, 2.5 g three times per day after meals, and a losartan potassium tablet dummy 100 mg/day in the morning.

Losartan group: a losartan potassium tablet given orally, 100 mg/day in the morning and a *huangkui* capsule dummy at 2.5 g three times per day after meals.

*Abelmoschus manihot* (AM): *huanghui* capsule (Jiangsu Suzhong Pharmaceutical Group Co., Ltd.), 0.5 g × 30 capsules/box. A *huangkui* capsule is a single, plant drug extract of *Flos Abelmoschus manihot*. The main composition is of flavonoids. Content: dry extract (powder), 80%; magnesium stearate, 3%; and calcium hydrogen phosphate, 17%. The medicinal parts are the corolla with the stamens and the style. The plant is picked in early August to late October (flowering period), undergoes alcohol extraction into ambrette fluid extract, and is then vacuum-dried and crushed into a dry-extract powder. Pharmaceutical preparation does not involve boiling. The *huanghui* capsule was approved by the China Food and Drug Administration in 1999 (Z19990040, approval date: 13 August 1999).

Losartan potassium (Hangzhou MSD Pharmaceutical Co., Ltd.), 100 mg × 7 capsules/box.

The *Huanghui* capsule dummy and the losartan potassium dummy are produced by Jiangsu Suzhong Pharmaceutical Group Co., Ltd.

Treatment continues for 48 weeks. Patients whose blood pressures are >140/90 mmHg after treatment will be given calcium channel blockers. Appropriate treatment is also given when patients develop hyperlipidemia, infection, or a hypercoagulable state. Glucocorticoids and immunosuppressive agents are prohibited. To improve adherence to intervention protocols, patients will be asked to take back the drug kit at every visit to exchange the new drug and whether the drug has been taken will be recorded.

### Study outcomes

#### Primary and secondary outcome measure

The primary outcome is the change in 24-h proteinuria from baseline after 48 weeks of treatment. For this measurement, patients are instructed to collect urine over 24 h (from 07:00 to 07:00 the next day). Urine output and the total amount are measured and recorded. Twenty-four-hour urinary protein excretion is calculated based on the concentration and 24-h urine volume. The secondary outcome measures are the change in eGFR from baseline after 48 weeks treatment and the incidents of endpoint events (proteinuria ≥3.5 g/24 h, doubling of serum creatinine, or receiving blood purification treatment). All the urine and blood samples are delivered to the central laboratory within 4 weeks for testing.

#### Other measurements

The patients’ general condition, demographic data, clinical history, physical examination, blood pressure and renal biopsy report are recorded. Laboratory assessments include routine urine test, routine blood test, blood biochemical tests (alanine aminotransferase, aspartate aminotransferase, triglyceride, cholesterol, low-density lipoprotein level, total bilirubin, direct bilirubin, gamma glutamyl transpeptidase, total protein, albumin, serum creatinine, blood urea nitrogen, uric acid, blood glucose and potassium). Enrolled patients also undergo electrocardiogram and chest X-ray examinations. Central laboratory tests include 24-h urinary proteinuria, urine routine test, serum cystatin C and high-sensitivity C-reactive protein. The urine and blood samples are both stored in a −80 °C refrigerator at central laboratory and participating centers.

### Safety

Safety evaluation includes the patients’ general condition, the incidence of adverse events, and laboratory assessments. Adverse events and SAEs are defined according to the definitions of Good Clinical Practice (GCP) by the China Food and Drug Administration (CFDA) [14].

### Participant follow-up

The enrollment process includes a screening visit to assess eligibility and obtain the informed consent and collection of clinical and demographic information. After enrollment, participants are evaluated at visit 1 (baseline visit), visit 2 (4 weeks), visit 3 (12 weeks), visit 4 (24 weeks) and visit 5 (36 weeks) and visit 6 (48 weeks) with similar data collection as performed in the baseline visit (Table 1).

**Table 1 Tab1:** Study visits

Item	Screening visit	V1	V2	V3	V4	V5	V6
Visit							
Time	−1w	0w ± 7d	4w ± 7d	12w ± 7d	24w ± 7d	36w ± 7d	48w ± 7d
Confirm eligibility	√	√					
Written informed consent	√						
Clinical and demographic information	√	√					
Physical examination	√	√	√	√	√	√	√
Signs and symptoms	√	√	√	√	√	√	√
24-h urinary proteinuria	√	√	√	√	√	√	√
24-h urine creatinine	√	√	√	√	√	√	√
Routine urine test	√	√	√	√	√	√	√
Urine pregnancy test		√					
Routine blood test		√	√	√	√	√	√
Blood biochemical tests		√	√	√	√	√	√
eGFR	√	√	√	√	√	√	√
Serum cystatin C and high-sensitivity C-reactive protein		√			√		√
Electrocardiogram and		√					√
Chest X-ray examinations		√					√
Drug distribution		√	√	√	√	√	
Drug combination		√	√	√	√	√	√
Adverse event			√	√	√	√	√
Exit criteria assessment			√	√	√	√	√

Note: the urine pregnancy test is screened in fertile women aged from 18 to 50 years

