#### Harms

Potential adverse events include dizziness, gastrointestinal discomfort, rash, itching, amenorrhea and cough. In the process of the clinical trial, any SAEs must be immediately reported to the principal investigator, the Medical Ethics Committee of the Chinese People’s Liberation Army General Hospital, and to Safety Supervision of CFDA within 24 h. At the same time, the researchers must fill in the record of SAEs including the time that the SAEs occur, their severity and duration and the measures and outcome. Adverse events are recorded every 4 weeks from the baseline visit until the final visit. SAEs are recorded up to 30 days after the final visit.

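### Pregnancy is an exit criterion assessed at V2–V6 and drug is re-dispensed at V2–V5, but the only scheduled pregnancy test is at V1

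*Protocol article*

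**What the plan says.** The exit criteria (section Eligibility, exclusion and exit criteria) end with "9) pregnancy during the trial". Pregnant women are also excluded at entry.

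Table 1 (section Participant follow-up) sets the visit schedule:

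- The row "Exit criteria assessment" is ticked at V2 to V6 (weeks 4, 12, 24, 36 and 48).
- The row "Drug distribution" is ticked at V1 to V5 (weeks 0, 4, 12, 24 and 36).
- The urine pregnancy test row is ticked at V1 only. Its footnote reads "Note: the urine pregnancy test is screened in fertile women aged from 18 to 50 years".

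The text above the table describes later visits as similar to baseline but refers to Table 1 for the content, where the V2–V6 cells of this row are empty. The laboratory list under Other measurements contains no pregnancy test.

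The Harms section states: "Potential adverse events include dizziness, gastrointestinal discomfort, rash, itching, amenorrhea and cough". It adds: "Adverse events are recorded every 4 weeks from the baseline visit until the final visit".

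**The concern.** The plan requires a pregnant participant to leave, and sets five visits at which that is to be judged, but schedules no objective test at any of them. The exit criteria that rest on a measurement are treated differently. Proteinuria, serum creatinine and potassium are measured at every post-baseline visit, and blood pressure can be taken at the physical examination ticked at each visit. For pregnancy, the test is already in the protocol but is not used after week 0.

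What remains is enquiry: self-report, signs and symptoms, and adverse event recording. Here that is a weak filter, because amenorrhea and gastrointestinal discomfort are both on the list of potential adverse events. A missed period or nausea can be written down as a drug effect, and no scheduled test settles the matter before the next supply is handed out. The trial is double-blind, so the site does not know which drug it is dispensing.

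What is at stake is participant safety and consistent use of an exit criterion. Sample size, power and the efficacy analysis are unaffected.

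**Working it through.** **Counts from Table 1.** There is one scheduled pregnancy test (week 0). There are five exit assessments after baseline, none with a test, and four re-dispensing visits, none with a test. The protocol states no figure of its own to reproduce.

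**Length of the next supply.** From V2 (week 4) to V3 (week 12) is 8 weeks. From V3 to V4, V4 to V5 and V5 to V6 it is 12 weeks each. Each visit has a window of ±7 days, so the gap can grow by 1 + 1 = 2 weeks, to 10 and 14 weeks.

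**What tests at V2–V6 would find.** The document gives neither the timing of conceptions nor test performance, so two assumptions are needed: conceptions are spread evenly over the 48 weeks, and a urine test turns positive 2 weeks after conception (3 weeks as the alternative). With a lag of 2 weeks:

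| Conception in weeks | First positive at | Delay range (weeks) | Mean delay (weeks) |
|---|---|---|---|
| 0–2 | V2 (week 4) | 2–4 | 3 |
| 2–10 | V3 (week 12) | 2–10 | 6 |
| 10–22 | V4 (week 24) | 2–14 | 8 |
| 22–34 | V5 (week 36) | 2–14 | 8 |
| 34–46 | V6 (week 48) | 2–14 | 8 |

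- Found by V6: 46/48 = 96%.
- Mean delay: (2×3 + 8×6 + 36×8)/46 = 342/46 = 7.4 weeks.
- Longest delay with windows: 12 + 1 + 1 + 2 = 16 weeks.
- First positive at a dispensing visit (V2–V5): 34/48 = 71%.

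With a lag of 3 weeks, the conception intervals become 0–1, 1–9, 9–21, 21–33 and 33–45:

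- Found by V6: 45/48 = 94%.
- Mean delay: (1×3.5 + 8×7 + 36×9)/45 = 383.5/45 = 8.5 weeks.
- Longest delay: 12 + 1 + 1 + 3 = 17 weeks.
- First positive at a dispensing visit: 33/48 = 69%.

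**Gain over enquiry.** The figures above describe testing alone. To credit the existing enquiry, suppose that it finds every pregnancy more than 4 weeks after conception and none earlier. The test then adds only the pregnancies between the lag and 4 weeks old at a dispensing visit:

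- Lag 2 weeks: 2 weeks of conceptions at each of 4 visits, 8/48 = 17%.
- Lag 3 weeks: 1 week at each of 4 visits, 4/48 = 8%.

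The 71% (69%) applies only if enquiry finds no pregnancy at all, so it is an upper bound.

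**Exposure avoided per case.** This is about 4 weeks if the next 4-weekly adverse event recording finds the pregnancy. It is up to 12 weeks, or 14 with windows, if the pregnancy is found only at the next visit.

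**The case against.** The best case against has four parts.

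*The plan does not contradict itself.* An exit criterion need not have its own test. Serious adverse events, protocol breach and withdrawal are reported events too, and pregnancy can be identified at V2–V6 by asking. This is correct: the criterion can be applied as written. The point is about how reliably it is applied.

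*Safeguards may sit elsewhere.* The consent form and full protocol are not shown, and may contain contraception advice or an instruction to test when a period is missed. That is possible. But Table 1 is presented as the visit schedule and has a row for this test with its own footnote. The blank cells are part of a stated schedule, and the gap is not a detail lost in condensing.

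*Listing amenorrhea may help.* Staff who ask about it every 4 weeks may be prompted to test. This is fair, and it is why the gain is given as a range. But nothing in the document requires a test when amenorrhea is reported.

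*The size is uncertain and the remedy broad.* Every percentage is conditional on a conception, and the document gives neither the number of fertile women nor a pregnancy rate. That limit stands. It is also true that a V6 test stops no supply, and that the 12/48 = 25% of conceptions first positive there (2-week lag) count towards the 96% but not towards the 71%. V6 still has an exit assessment, and a test there would identify late pregnancies exposed to study drug.

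**Conclusion.** The concern holds as a safety gap in the visit schedule that should be fixed. No test is scheduled during 48 weeks of treatment, although exit for pregnancy is judged five times and drug is re-dispensed four times. The reading of Table 1 needs no assumption.

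The size does. Given evenly spread conceptions and a 2-week (3-week) lag, adding the test would stop a further supply in 17% (8%) of on-treatment conceptions if enquiry is perfect after 4 weeks and blind before. The figure could be as high as 71% (69%) if enquiry finds nothing. No absolute number can be given, and the document has no data on fetal risk with either drug. The protocol's own requirement that a pregnant participant leave is enough to justify the test.

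**What to change.** Extend the urine pregnancy test row of Table 1 to V2–V6 for fertile women aged 18 to 50. At V2–V5, read the result before drug is dispensed.

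Use a dipstick read at the site. The test should not join the central laboratory panel ("Central laboratory tests include 24-h urinary proteinuria, urine routine test"), because of the transport time: "All the urine and blood samples are delivered to the central laboratory within 4 weeks for testing". A central result could arrive after the drug has been handed out.

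The cost is a short amendment by the route described under Dissemination (Executive Committee discussion and Ethics Committee approval), its rollout to the centers, and up to five dipsticks per fertile woman. Table 1 already has urine collected at every visit, so no extra visit is needed. By the dates under Trial status, recruitment began in October 2015 and 912 of about 1600 patients were in by 13 June 2016. That is less than 48 weeks, so no participant could yet have completed treatment, and an amendment at that date would have reached current as well as future participants.

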### Sample size

The sample size determination is based on the primary outcome 24-h proteinuria. The alpha level is set to a one-sided value of 0.025%. We assume that the expected decline of 24-h proteinuria is 1600 ± 500 mg. The noninferiority margin (0.5 of the estimated standard deviation) is 250 mg. With a 15% dropout rate, to enroll 124 patients per arm will offer 95% power to demonstrate noninferiority of AM compared to losartan with a 250-mg noninferiority margin. At the same time, based on the observation of safety, sample size expanded to 800 patients per arm will offer 80% power to detect the rare adverse reactions (incidence <0.5%) at least in one patient.

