### Randomization procedure, allocation concealment, implementation of blind method

Consecutive numbers are assigned to each participating center according to a center-stratified random order generated by SAS 9.4 Proc Plan. Peking University Clinical Research Institute takes the responsibility of generating the allocation sequence and an interactive voice-response or web-response system will be used to assign each patient a number and group. The centers then randomly assign patients to the AM or losartan potassium treatment group. The allocation ratio is 1:1. The test uses a double-dummy drug; therefore, in the whole course of the trial, the patients, the doctors and the statistical analysts of the trial are unaware of the treatments. In patients with SAEs, an emergency unblinding procedure will be initiated.

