### Statistical methods

The statistical analysis plan will be decided before database lock and unblinding of the trial. Statistical analysis for the trial will be performed by the Peking University Clinical Research Institute. Statistics software SAS 9.4 will be used for the data analysis. Data analysis follows the principles of intention-to-treat analysis (ITT). The full analysis set is defined as all randomly assigned patients with both a baseline and a post-baseline assessment. Last observation carried forward (LOCF) will be used to handle the missing data. Categorical variables are presented as counts with percentages and compared by the chi-square test or Fisher’s exact test. Continuous variables are presented as mean with standard deviation and compared by *t* test if the variables are normal distribution or Mann-Whitney *U* test if the variables are non-normally distributed. A *t* test (two independent samples) will be conducted to compare the primary and secondary outcomes. An analysis of covariance (ANCOVA) model for the primary outcome will be conducted considering baseline proteinuria and study center effect. The LS-means and 95% LS confidence intervals will be generated.

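### The one-sided alpha is printed as 0.025%, which cannot be reconciled with the protocol's own 124 per arm; that figure requires 0.025 (2.5%)

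*Protocol article*

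**What the plan says.** The Sample size section of the protocol article gives the error rate and all the planning inputs in one paragraph:

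- Error rate: "The alpha level is set to a one-sided value of 0.025", and the number is followed by a percent sign. Read literally, this is 0.00025. No other significance level appears in the article.
- Effect and spread: "We assume that the expected decline of 24-h proteinuria is 1600 ± 500 mg".
- Margin: "The noninferiority margin (0.5 of the estimated standard deviation) is 250 mg".
- Resulting size: "With a 15% dropout rate, to enroll 124 patients per arm will offer 95% power to demonstrate noninferiority of AM compared to losartan".
- Enlargement for safety: "sample size expanded to 800 patients per arm will offer 80% power to detect the rare adverse reactions".

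The section on randomization adds "The allocation ratio is 1:1". The Statistical methods section, after naming an ANCOVA for the primary outcome, says "The LS-means and 95% LS confidence intervals will be generated".

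**The concern.** The paragraph gives enough inputs to check its own arithmetic. A one-sided level of 0.00025 is a hundred times smaller than 0.025 (0.025/0.00025 = 100) and should require far more than 124 patients per arm for 95% power. If so, the stated alpha and the stated sample size cannot both be right.

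At stake is the error rate of the primary noninferiority test. It is the only such rate in the article, so a reader cannot learn the intended value without rebuilding the sample size.

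**Working it through.** **Inputs.** From Sample size: SD 500 mg, margin 250 mg, power 95%, dropout 15%, 124 per arm, enlarged to 800 per arm. From the randomization section: 1:1 allocation. Assumption: true difference between arms 0, because a single expected decline is given for both arms.

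**Formula.** Evaluable patients per arm (normal approximation): n = 2 × (z₁₋α + z₀.₉₅)² × (SD/margin)², with (500/250)² = 4 and z₀.₉₅ = 1.645. Enrolled = n/(1 − 0.15). The exact version replaces the normal distribution with the noncentral t.

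**Step 1: reproduce the 124, using one-sided 0.025.**
- Normal: 2 × (1.960 + 1.645)² × 4 = 103.96, so 104 evaluable; 104/0.85 = 122.4, so 123 enrolled.
- Noncentral t: 105 evaluable (power 95.0%); 105/0.85 = 123.5, so **124 enrolled**.

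The t version matches the stated figure exactly, and the normal version is one patient lower.

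**Step 2: the level as printed, one-sided 0.00025 (z = 3.48).**
- Normal: 210.2, so 211 evaluable; 211/0.85 = 248.2, so 249 enrolled.
- Noncentral t: 214 evaluable; 214/0.85 = 251.8, so **252 enrolled**.

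This is about twice the stated number.

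**Step 3: power of the stated size at the printed level.** With n evaluable per arm the standardized effect is 0.5 × √(n/2).
- n = 105: 0.5 × √52.5 = 3.62. Normal power is Φ(3.62 − 3.48) ≈ 56%; noncentral t gives 53.6%.
- n = 124 with no dropout at all: 68% (normal) or 66% (t).

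Neither is near 95%.

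**Step 4: other readings.** Enrolled per arm (normal to t), dividing by 0.85:

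| One-sided alpha | Enrolled per arm |
|---|---|
| 0.05 | 103 to 104 |
| 0.025 | 123 to 124 |
| 0.0125 | 143 to 145 |
| 0.0005 | 230 to 233 |
| 0.00025 | 249 to 252 |

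Inflating by 1.15 instead of dividing by 0.85 gives 243 to 247 at 0.00025, and 120 to 121 at 0.025. Of the levels tried, only 0.025 yields 124.

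**Step 5: effect at the planned enrolment.** 800 × 0.85 = 680 evaluable per arm.
- Power: 0.5 × √(680/2) = 9.22. Subtracting 3.48 leaves 5.74, and subtracting 1.96 leaves 7.26. Power is above 99.9% at either level.
- Success threshold: SE = 500 × √(2/680) = 27.1 mg. At 0.025, noninferiority is shown if the observed AM shortfall is below 250 − 1.96 × 27.1 ≈ 197 mg. At 0.00025 it must be below 250 − 3.48 × 27.1 ≈ 156 mg.

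The two levels therefore give different conclusions only for an observed shortfall of about 156 to 197 mg.

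**Step 6: the interval.** A two-sided 95% interval pairs with one-sided 0.025. One-sided 0.00025 would pair with a 1 − 2 × 0.00025 = 99.95% interval.

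**The case against.** The strongest reply is that this is a unit slip, probably a stray percent sign, which the rest of the paragraph exposes. Nothing in the article suggests that 0.00025 was intended or used in the calculation. That stands. It makes the correction simple, but the printed level remains wrong and nothing else in the article overrides it. Nor is this a matter left to the statistical analysis plan, because the article does state a level.

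Three stronger readings are tempting, and the documents do not support them.

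- *The trial is underpowered.* A reader might infer this from the 54% power or the 252 per arm. Those figures describe 124 enrolled per arm, whereas the trial plans 800 per arm and has ample power at either level under its own assumptions.
- *The planned 95% interval independently contradicts the alpha.* The Statistical methods section says only that such intervals will be produced. It does not make them the noninferiority criterion, and a 95% reporting interval can coexist with a stricter test. The interval is supporting evidence; the sample-size arithmetic carries the point.
- *The trial's conclusion hangs on which figure is followed.* This is possible in principle, but only in the band of about 156 to 197 mg. Its lower end is more than five standard errors from the planned difference of zero (156/27.1 = 5.8).

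**Conclusion.** The point holds as a wrong statement of the primary test's error rate. One-sided 0.025% is incompatible with 124 per arm for 95% power, and one-sided 0.025 (2.5%) reproduces that number. The sample-size calculation appears to have been run correctly; the printed level is what is wrong.

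The practical size is limited. Enrolment and power are unaffected at 800 per arm. The declared critical value is 3.48 where 1.96 fits the calculation, with consequences only in the band shown in step 5.

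The reproduction rests on a true difference of 0 and, for an exact match, on the t-based sample size. The band rests also on the protocol's SD of 500 mg and on 15% dropout, and would move if either differed.

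**What to change.** In Sample size, restate the level as one-sided 0.025 (2.5%). Optionally add that this corresponds to the relevant bound of a two-sided 95% confidence interval; that is a clarification and does not follow from the error itself.

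The cost is one line, with no change to design, enrolment or analysis. It is best made before database lock and unblinding, by when the article says the analysis plan will be settled. A correction made once results are known could look like a hundred-fold loosening of alpha.

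### The safety sample-size sentence pairs 800 per arm and 80% with an incidence (<0.5%) that does not fit; 80% holds only at about 0.2%

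*Protocol article*

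**What the plan says.** The Sample size section of the Protocol article makes two calculations. The first, for the primary outcome, assumes a standard deviation of 500 mg and a noninferiority margin of 250 mg: "With a 15% dropout rate, to enroll 124 patients per arm will offer 95% power". The second is for safety: "based on the observation of safety, sample size expanded to 800 patients per arm", the reason given being that "800 patients per arm will offer 80% power to detect the rare adverse reactions (incidence <0.5%) at least in one patient".

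The detection criterion is explicit (at least one case) and the number is per arm. The only incidence printed is an upper limit, below 0.5%. The section does not say whether the 15% dropout also applies to the safety figure. The randomization section fixes equal arms ("The allocation ratio is 1:1"), which agrees with the planned total of about 1600.

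**The concern.** The probability of seeing at least one case depends only on the number of patients and the true incidence. A power figure for this criterion therefore needs one design incidence, and an open-ended range cannot supply it. A reader will naturally take the one printed number, 0.5%, as the incidence at which 800 patients give 80%. That is well off.

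The sentence matters because it is the only reason given for enrolling about 1600 patients instead of 2 × 124 = 248. It also tells the reader how sensitive the trial is to rare reactions. Someone who takes 80% to cover everything under 0.5% will be too confident about reactions rarer than about 0.2%. Someone who takes 0.5% as the 80% limit will underrate the trial.

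**Working it through.** **Inputs, all from the Sample size section:** n = 800 per arm; at least one case; stated probability 80%; incidence below 0.5%; dropout 15%, stated for the efficacy calculation only. If dropout is applied to safety as well, 800 × 0.85 = 680 per arm.

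**Formula:** P(at least one case) = 1 − (1 − p)^n.

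**Step 1: the plan's own figure at the printed limit.** 1 − 0.995^800 = 0.982. The stated 80% is not reproduced; the gap is about 18 percentage points.

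**Step 2: rates at and below the limit.**

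| True incidence | n = 800 | n = 680 |
|---|---|---|
| 0.5% | 98.2% | 96.7% |
| 0.4% | 96.0% | 93.5% |
| 0.3% | 91.0% | 87.0% |
| 0.2% | 79.8% | 74.4% |
| 0.1% | 55.1% | 49.4% |
| 0.05% | 33.0% | 28.8% |

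**Step 3: the incidence at which the probability is exactly 80%.** p = 1 − 0.2^(1/n). For n = 800 this is 0.00201, or 0.20%. For n = 680 it is 0.00236, or 0.24%.

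**Step 4: the number that 80% at exactly 0.5% would need.** ln(0.2)/ln(0.995) = 321.1, so 322 per arm, or 322/0.85 = 378.8, so 379 with 15% dropout.

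**Step 5: other readings at 0.5%.**
- Both arms pooled (1600): 99.97%.
- At least one case in each arm: 0.982² = 96.4%.
- At least two cases in 800: 90.9%; at least three: 76.3%.
- At least two cases in 680: 85.4%.
- A comparison of 0.5% with zero, 800 per arm: 51.7% two-sided, 64.0% one-sided.

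None comes within 2 points of 80%. Pooling both arms does give 79.8% at 0.1%, but the sentence is worded per arm.

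**Step 6: does the rest of the section reproduce?** Reading the one-sided level as 0.025, n = 2 × (1.960 + 1.645)² × (500/250)² = 104 per arm, and 104/0.85 = 122.4, so 123 against the 124 stated. The efficacy figure is consistent, so the mismatch is confined to the safety sentence.

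**Step 7: zero-event bound, if one is wanted.** The one-sided upper 95% limit with no cases is 1 − 0.05^(1/n): 0.37% for 800 and 0.44% for 680.

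**The case against.** The strongest reply is that the text prints an inequality, and 0.2% satisfies it. At that round value 800, 80% and at least one case agree almost exactly. The limit of 0.5% may only describe what counts as rare, with 0.2% used in the calculation. The article is also condensed, and the full protocol may name the rate. Much of this stands: the match at 0.2% is a good reason not to call 800 an error. But 0.2% appears nowhere in the article, and the article chose to print a sample size, a power and a rate that do not agree. That the full protocol may be clearer does not repair the printed sentence.

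Three stronger readings are tempting, and the documents support none of them.

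- A reader might infer that 800 per arm is unjustified because 322 would do. That holds only if the target was 80% at exactly 0.5%, which the section does not say.
- A reader might infer that the trial is too small for its safety aim. At 0.5% the stated 80% is conservative. It overstates the probability only for rates below about 0.2%.
- A reader might infer that the trial will wrongly claim to exclude certain reactions. The sentence speaks only of seeing at least one case and makes no claim to rule out any incidence. The Safety section does not use the 80% figure.

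**Conclusion.** The sentence is wrong as written, and the fault is narrow. With 800 per arm the probability of at least one case is 98.2% at 0.5%, 80% at about 0.2% and 55% at 0.1%, so the stated 80% is true neither at the printed limit nor throughout the range below it. The likeliest explanation is an unstated design incidence of 0.2%. That is an inference from the arithmetic, not something the article says.

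The sample size need not change, and the noninferiority calculation is unaffected. What fails is that the stated reason for going from 124 to 800 per arm cannot be reproduced from the printed figures. This is a correction of wording with a numerical consequence, not a design flaw.

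The result assumes independent patients with a common incidence, all of them evaluable. The 680 scenario is an assumption, because the article ties dropout to the efficacy calculation and patients who leave early still contribute some exposure.

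**What to change.** Replace the safety sentence with wording such as:

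> 800 patients per arm give about 80% probability of observing at least one case of an adverse reaction with true incidence 0.2% (98% at 0.5%, 55% at 0.1%).

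Then state whether the 15% dropout is meant to apply. If it leaves 680 evaluable per arm, add that the probability at 0.2% is about 74% and that 80% is reached at about 0.24%. If the sponsor's records show that 0.5% was the design incidence, keep it and change the power to 98%.

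A zero-event bound is optional. If given, label it one-sided 95% and base it on the number actually exposed.

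The cost is one sentence, carried into any other trial document that repeats the claim. Enrolment and analysis do not change.
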